### Plans to promote participant retention and complete follow-up {18b}

The clinical research team will discuss appointment dates with participants to ensure suitability, provide appointment dates in advance and address any transport or accessibility needs. Dates and times can be provided in writing. Reminder phone calls will be made prior to leukapheresis and baseline appointments. Future appointment dates and times will be re-discussed at each appointment.

Participants can withdraw from the study at any time without providing a specific reason. Data collected to the point of withdrawal will be retained and utilised, although participants may request to have stored samples destroyed. Participants withdrawing will be asked for written permission to collect and use data from routine clinical follow-up for the period of their intended participation. Where the TolDC_CitPep_ have been administered, contact in line with a participant’s week 12 assessment will be attempted to check for adverse reactions (ARs).

### Data management {19}

All data for an individual participant will be recorded in the study-specific electronic Case Report Form (eCRF) set up using Sealed Envelope’s™ Red Pill system which will include tested range checks for numerical data values. Access to the study database will be password-limited, with task-specific restrictions. Only staff formally delegated to do so will have access to the database.

Data will be handled, computerised and stored in accordance with the UK Data Protection Act 2018, UK GDPR, the latest GCP Directive (2005/28/EC) and local site policy. Paper copies of study-related documentation will be annotated, signed, dated and filed in the Investigator Site File (ISF). The signed ICF, eligibility forms, GP letter and RA assessments will be uploaded to the participant’s medical notes.

All study documentation will be archived for 30 years in accordance with UK GCP legislation and local SOPs.

### Confidentiality {27}

Participant identification on the eCRF will be via a unique study identifier number. A record linking the participant’s name to the unique study identifier number will be held in a locked room at the study site. Only the Principal Investigator (PI) and appropriately delegated staff will have access to source data and the ISF for the purpose of conducting the study.

### Plans for collection, laboratory evaluation and storage of biological specimens for genetic or molecular analysis in this trial/future use {33}

NHS laboratory and tissue typing bloods

Participants will provide NHS laboratory blood samples, which will be analysed in local Trust laboratories and then discarded. These will be collected and tested as per Table 2 below.

**Table 2 Tab2:** NHS laboratory blood samples

Blood set	Tests to be performed	Time points collected	Participants
Set 1	• Cyclic Citrullinated Peptide Antibody (Anti-CCP) • Rheumatoid factor (RhF) • Full blood count (FBC) • Erythrocyte sedimentation rate (ESR) • Coagulation Screen (with derived Fibrinogen) • International normalised ratio (INR) • Urea and electrolytes (U + E) • Magnesium (Mg) • Adjusted calcium • Liver function test (LFT) • C-reactive protein (CRP) • Human immunodeficiency virus (HIV) • Hepatitis B + C • Human T cell Leukaemia Virus (HTLV) 1 + 2 • Syphilis • Cytomegalovirus (CMV) • HLA DRB1 tissue type (except where tissue type is already known) • Follicle-stimulating hormone (FSH) *	Screening	All * FSH can be considered to prove post menopausal state in women < 50 years who have been amenorrhoeic for 12 months and would prefer testing to using contraception for the duration of the study on discussion with the investigator
Set 1B	• HIV • Hepatitis B + C • HTLV 1 + 2 • Syphilis • CMV	Secondary screening visit	Those screened > 38 days before scheduled baseline visit
Set 2	• FBC • U&E • LFT • Phosphate • Mg • Adjusted calcium • Group + Save • HIV • Hepatitis B + C • HTLV 1 + 2 • Syphilis	Leukapheresis visit	All, except participants randomised to Group 5 (control group)
Set 3	• FBC • U&E • LFT • CRP • ESR	Baseline, follow-up visits 1, 2 and 3	All
Set 4	• FBC • U&E • LFT • CRP • ESR • RhF • ACPA	Follow-up visit 4	All
Set 5	• FBC • U&E • LFT • CRP • ESR • Any additional test at the discretion of the investigator	Flare visit	Those completing a flare visit

Peripheral blood research biomarkers

Research blood samples will be obtained at baseline and weeks 1, 3 and 6. This will involve the collection at each visit of 108 ml of blood in a combination of EDTA and serum separator tubes. Some of this sample will be studied immediately within the research laboratory and the remainder processed and cryopreserved for analysis following study completion.

Lymph node aspirate samples

Lymph node aspirate samples will be obtained by an experienced radiologist using direct ultrasound visualisation to aspirate up to 5 lymph nodes using a 23 Gauge needle and 3-ml syringe under tension. Samples will be immediately passed to a member of the study team for processing and cryopreservation for analysis following study completion.

## Statistical methods

### Statistical methods for primary and secondary outcomes {20a}

AuToDeCRA-2 is not powered for formal statistical significance. Nonetheless, a statistical analysis plan will be developed during the study.

The analysis population will include all subjects who have received their allocated intervention. For AE reporting, the analysis population will be all individuals who provide consent, whether or not they subsequently receive TolDC_CitPep_.

Demographic characteristics, medical history and clinical characteristics collected at screening will be summarised descriptively and tabulated. For categorical variables, the frequency and percentage in each group will be reported. For continuous variables the mean, standard deviation and/or median and interquartile range will be reported.

Within each arm (*n* = 4), we will assess whether there are any consistent trends in the parameters being measured, both for primary and secondary outcomes, and we will compare each of the 4 intervention arms against the control group and each other for primary and secondary outcomes.

Summary statistics capturing differences in immune biomarkers (expressed as percentages, stimulation indices, titres, etc.) and clinical outcomes (descriptive and numeric) will be tabulated and presented graphically. Longitudinal analysis will be performed to compare samples following TolDC_CitPep_ administration at baseline. Given the low participant number in each group (4), no formal statistical testing will be performed other than to explore analysis methods, identify prospective transformations of the data, identify key prospective time points and obtain estimates of the variability in both primary and secondary measures to inform the design of a future efficacy study. Estimates of variability will be based on a mixed effects model including participant, route of administration and sampling time point.

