### Objectives {7}

AuToDeCRA-2 is designed to demonstrate and compare immunomodulation using synthetic citrullinated peptide-loaded TolDC (TolDC_CitPep_) administered via three distinct routes: intra-nodal, intra-articular, intra-dermal and in the case of intra-nodal administration, at a low and a high dose. The rationale for loading TolDC with citrullinated peptides is explained in section ‘Intervention description {11a}’.

Table 1 outlines the study objectives which will be achieved by comparing baseline data with follow-up data at 1, 3, 6 and 12 weeks.

**Table 1 Tab1:** Study objectives

Primary objectives	Secondary objectives	Exploratory objectives
• To seek signals of immune modulation when TolDC_CitPep_ are administered to participants with RA using immune state biomarkers performed on peripheral blood samples at baseline, 1, 3 and 6 week follow-up and participant lymph node aspirates at baseline and 1 week follow-up	• To seek signs of clinical efficacy when TolDC_CitPep_ are administered to participants with RA using ACR 20, 50 and 70, DAS-28, and components thereof at baseline and 1, 3, 6 and 12 week follow-up • To provide further evidence of TolDC_CitPep_ safety using reported adverse events (AEs) at baseline, 1, 3, 6, and 12 week follow-up • To provide further evidence of participant acceptability of TolDC_CitPep_ therapy for RA using a Participant Acceptability questionnaire at 12 week follow-up	• To link signals of immune modulation with signs of potential efficacy of TolDC_CitPep_ using potential associations between immune modulation measures and evidence of efficacy for the three different routes of TolDC_CitPep_ administration (and, in the case of intra-nodal injection, for the two doses administered) • To compare intra-nodal (low and high dose), intra-dermal and intra-articular injection with regards to primary and secondary objectives, and feasibility

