## Interventions

### Explanation for the choice of comparators {6b}

The optimal route for TolDC administration is not clear. The DC-T-cell interaction is believed to occur primarily in lymph nodes. We hypothesise that the route of injection most likely to ensure the TolDC reach a lymph node is direct injection into lymph nodes, but intra-nodal injection is a less convenient route of delivery, requiring ultrasound equipment and a trained operator. AuToDeCRA-2 will therefore compare direct intra-nodal injection with alternative routes that should enable cells to reach disease-relevant lymph nodes. Intra-dermal is the most well studied route of administration [5, 6, 15] for therapeutic DC and does not require specialised equipment. In contrast, intra-articular injection requires specialised equipment and operators, but it is possible that the joint-relevant immune system is best accessed via this route. 10^7^ TolDC will be administered via all routes to provide a direct comparison, being the highest dose that was administered in AuToDeCRA. A lower dose of 10^5^ TolDC will also be administered intra-nodally as injecting directly into a lymph node may require fewer cells to achieve a therapeutic effect.

The fifth arm is standard care. Standard care was chosen over placebo so that participants would not need to undergo unnecessary leukapheresis or administration procedures. Standard care involves no leukapheresis visit and no administration of TolDC_CitPep_ but all other study procedures remain the same.

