### Criteria for discontinuing or modifying allocated interventions {11b}

There are no plans to modify or permit modification of allocated interventions. The intervention will not be administered if the TolDC_CitPep_ do not meet stringent release criteria.

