**Fig. 2 Fig2:**
[figure not shown]
Schedule of events

Screening will take place between day − 150 and day − 10. If screening takes place between day − 150 and day − 39 then a secondary screening visit will occur between day − 38 and day − 10. This is to ensure that the participant remains eligible and to allow for safety blood sampling in line with leukapheresis and TolDC production facility SOPs.

After screening and randomisation (and leukapheresis for those receiving TolDC_CitPep_), participants will attend for baseline (day 0) clinical and immunological assessments. All participants will provide a blood sample and an ultrasound-guided fine needle aspirate from inguinal lymph nodes. These blood and lymph node aspirate samples will contribute to the immunological endpoints described above. Participants in intervention arms will then receive TolDC_CitPep_ at the allocated dose and via the allocated administration route.

Participants will be followed up on four occasions at 1, 3, 6 and 12 weeks after the baseline visit. Clinical assessment and blood sampling will take place at each visit. At the week 1 follow-up visit, all participants will undergo a second lymph node ultrasound-guided fine needle aspirate.

If, during the follow-up period, a participant suffers deterioration in their arthritis symptoms, they will attend for a ‘flare visit’. A full clinical assessment will be performed and, if a flare of RA is diagnosed, the participant managed appropriately at the discretion of the investigator, according to standard care. If therapeutic intervention is required for the flare, final samples will be taken for immunological endpoints and the participant will exit the study.

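### The main analysis set leaves out randomised participants who were not dosed, a loss only the active arms can suffer, and adverse events counted from consent need a post-dose summary beside them

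*Protocol article*

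**What the plan says.** Section {20a} of the protocol article names two populations. For the outcomes in general: "The analysis population will include all subjects who have received their allocated intervention". For harms: "For AE reporting, the analysis population will be all individuals who provide consent, whether or not they subsequently receive TolDC_CitPep". The same section says that every active arm will be compared with control and with the other active arms on primary and secondary outcomes.

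The order of events is given under Fig. 2: "After screening and randomisation (and leukapheresis for those receiving TolDC_CitPep_), participants will attend for baseline (day 0) clinical and immunological assessments". Section {11a} describes manufacture and release after leukapheresis, and section {11b} adds: "The intervention will not be administered if the TolDC_CitPep_ do not meet stringent release criteria". For the control arm, section {6b} states: "Standard care involves no leukapheresis visit and no administration of TolDC_CitPep_ but all other study procedures remain the same".

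Table 1 includes an exploratory comparison of routes and doses, "injection with regards to primary and secondary objectives, and feasibility". The acceptability outcome in section {12} covers leukapheresis as well as administration. The safety objective in Table 1 concerns the TolDC product. Section {22} records adverse events from consent, and serious adverse reactions from administration.

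**The concern.** Receipt of the allocated intervention is settled after randomisation, and it can fail for want of product only where there is a product. An active-arm participant whose cells are not released leaves the main set. A control participant has no matching step at which to leave. The active arms then consist of people whose cells could be collected, manufactured and released, and they are set against controls who were never tested in that way. If success in manufacture is related to immune state, background medication or disease activity, the contrast with control is no longer the one that randomisation set up. Describing a difference without testing it does not remove this.

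The set also loses information. Someone who went through leukapheresis and was then not dosed is among the most informative people on the acceptability of leukapheresis, and is left out of that outcome.

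The adverse event set raises a smaller question. The objective concerns the product, but counts that start at consent include events before dosing. Among these are leukapheresis events, which only the active arms can have. A between-arm difference in such counts would mix the effect of leukapheresis with the effect of TolDC.

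**Working it through.** **Inputs from the protocol article.** 20 participants, five arms, equal allocation; screening between day −150 and day −10; consent at the screening visit; leukapheresis at day −8; last follow-up at week 12.

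**Input assumed.** The probability p that a randomised active participant does not receive the allocated product. The document gives no rate, so I use 5% to 15%, independent between participants.

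1. Arm size: 20 / 5 = 4, which reproduces the figure in section {20a}. Active participants: 4 × 4 = 16.

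2. Effect of one failure: 1 / 4 = 25% of that arm.

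3. Chance that at least one of the 16 is dropped, 1 − (1 − p)^16:
   - p = 0.05: 1 − 0.95^16 = 0.560
   - p = 0.15: 1 − 0.85^16 = 0.926

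4. Chance that a given active arm falls below 4, 1 − (1 − p)^4:
   - p = 0.05: 1 − 0.95^4 = 0.185
   - p = 0.15: 1 − 0.85^4 = 0.478

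5. Expected number of active participants left, 16(1 − p): 15.2 at 5% and 13.6 at 15%. The control arm loses none of its 4 to this filter.

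6. Adverse event window. Follow-up after day 0 is 12 × 7 = 84 days. For one participant, the share of observed time before day 0 is:
   - screened at day −10: 10 / (10 + 84) = 11%
   - screened at day −150: 150 / (150 + 84) = 64%

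   These are the two ends of the screening window for a single person. They are shares of observation time, not of events, and they say nothing about the cohort average. Screening time applies to every arm; leukapheresis does not.

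7. Exposure. If nobody failed screening and everyone allocated product received it, 16 of 20 (80%) in the consent-based set would have had TolDC. Any screen failure or undosed participant lowers that share.

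**The case against.** The best defence is that the main set suits the main question. The primary objective asks what happens to immune markers when the cells are given. An undosed participant carries no information on that, and the study is exploratory with no formal testing beyond exploring methods and estimating variability. This stands for the biomarkers, and the set should be kept for them. It does not cover clinical outcomes or acceptability, which are compared under the same definition. Leukapheresis and manufacture are also described once for all active arms, so they should not favour one route over another. That too is fair, and it leaves the contrast with control as the main exposure.

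Several stronger readings go beyond the text:

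- A reader might infer that the two populations have been interchanged. They have not, and a swap would be wrong: outcomes in all consenters would include people never randomised, and harms in dosed participants alone would omit leukapheresis harms in those never dosed.
- A reader might infer that feasibility cannot be compared. Section {20a} does not assign feasibility to either set, section {21b} promises a CONSORT diagram that will show losses before dosing, and section {20c} promises an investigation of withdrawals and missed appointments.
- A reader might infer that adverse event percentages will be diluted by people never exposed. That follows only if events are pooled over all consenters. Section {20a} does not say so, and the outcome in section {12} is a number of events.
- A reader might take the leukapheresis-day bloods in Table 2 ("All, except participants randomised to Group 5 (control group") as a further hurdle. The table lists who is sampled and gives no pass or fail rule.

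Section {11c} also judges non-attendance after leukapheresis unlikely. That bears on attendance, not on release failure.

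**Conclusion.** The point holds in a limited form. As written, the main set rests on a one-sided exclusion after randomisation, while the same section compares each active arm with control. One failure costs a quarter of an arm. The chance of at least one among 16 is 56% to 93%, and of a given arm falling short 19% to 48%, but these depend wholly on the assumed 5% to 15%. The direction and size of any bias cannot be stated, because the document gives neither a failure rate nor its relation to outcome.

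The adverse event point is smaller. The consent-based population is a sound basis for a listing. On its own it does not answer a question about the product, since it includes events before dosing and leukapheresis events confined to the active arms. Separate reporting of serious adverse reactions from administration helps, but only for serious reactions.

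Neither point threatens the biomarker aim. Both call for added summaries, not for replacing either population.

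**What to change.** In the analysis plan, which section {20a} says is still to be developed, or in the protocol wording:

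1. Keep the received-intervention set for the mechanistic biomarker analysis.
2. Add a set of all randomised participants, as allocated. Use it, with the data available, to summarise clinical outcomes, acceptability and feasibility. Define feasibility as the proportion of randomised participants who received the full allocated product, with reasons where they did not.
3. Show by arm who was lost between randomisation and dosing.
4. Keep the adverse event listing from consent. Add a by-arm summary of events with onset from day 0 to week 12, in dosed participants against control over the same window.
5. Tabulate screening events and leukapheresis-phase events separately.

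The cost is some wording and one more set of tables. The undosed participants, probably few, will have incomplete data, and the tables should say so. Arm sizes in the all-randomised summaries stay at 4, with the number observed given beside each result.

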### Trial design {8}

AuToDeCRA-2 is a non-commercial, exploratory, unblinded, randomised experimental medicine study with 5 parallel groups of ACPA-positive RA participants in an allocation ratio of 1:1:1:1:1, with the aim of demonstrating and comparing immunomodulation by TolDC_CitPep_.

The study protocol follows the Standard Protocol Items: Recommendations for Interventional Trials (SPIRIT) 2013 statement. The study has been registered with ISRCTN [14999554].

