### Sample size {14}

There are no relevant background data available to power this study, which is exploratory and not powered for statistical significance. The sample size of 20 is based upon expected feasible recruitment into a complex experimental medicine protocol, based on prior experience from AuToDeCRA.

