We anticipate that recruitment of participants with few or no symptoms may present another challenge due to the intensive monitoring, the use of an experimental advanced therapy medicinal product (ATMP) and the involvement of procedures including leukapheresis. Consequently, a robust and multi-faceted recruitment plan has been developed. Limitations include the small number of participants; however, this is felt to be a realistic recruitment goal and adequate to address the aims of the study.

In summary, AuToDeCRA-2 is an early phase experimental medicine study of an ATMP with the main objectives being to compare routes of administration and to demonstrate the ability of TolDC_CitPep_ to induce immunomodulation. Knowledge gathered from this study will help define biomarker outcomes and address existing scientific gaps necessary to inform the design of future TolDC studies for RA and other conditions where restoration of immune tolerance is desired.

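### The primary objective names no route or dose, but every between-arm contrast named is four against four; a pooled TolDC-versus-control estimate should be added and the adequacy claim replaced by achievable precision

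*Protocol article*

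**What the plan says.** Table 1 under Objectives {7} gives the primary objective as "To seek signals of immune modulation when TolDC_CitPep_ are administered to participants with RA", using biomarkers in blood and lymph node aspirates. It names no route or dose. The exploratory column of the same table includes "To compare intra-nodal (low and high dose), intra-dermal and intra-articular injection", and the exploratory endpoints under Outcomes {12} repeat that status.

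Trial design {8} sets out "5 parallel groups of ACPA-positive RA participants in an allocation ratio of 1:1:1:1:1". Sample size {14} states that "The sample size of 20 is based upon expected feasible recruitment into a complex experimental medicine protocol" and that the study is exploratory and unpowered.

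Statistical methods {20a} plans four things:

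- a look for consistent trends within each arm of four;
- between-arm comparisons: "we will compare each of the 4 intervention arms against the control group and each other for primary and secondary outcomes";
- a longitudinal analysis of samples around TolDC_CitPep administration;
- a mixed model with participant, route and time point, whose stated purpose is to estimate variability.

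Formal testing is disclaimed except to explore methods and inform a later trial.

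The main Discussion summarises the study "with the main objectives being to compare routes of administration" as well as showing immunomodulation. Of the small sample it says "this is felt to be a realistic recruitment goal and adequate to address the aims of the study"; the Abstract makes the same adequacy statement.

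**The concern.** The between-arm contrasts that are named serve the exploratory objective. The controlled contrast closest to the primary objective, all treated participants against standard care, is not named, although the data for it will exist. The 16 treated participants are therefore used four at a time whenever the control group is the reference.

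Two consequences follow. A modest effect shared by all routes would be estimated less precisely than the data allow. And a wide interval between two routes could be read as a sign that they perform alike, because the Discussion promotes route comparison to a main objective and describes the sample as adequate for the aims.

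**Working it through.** **Inputs.** Five arms, equal allocation, 20 participants (Trial design {8}, Sample size {14}): 5 × 4 = 20, which reproduces the stated total. That gives 16 on TolDC_CitPep and 4 on standard care. The document gives no SD, significance level or power, so results are in units of the SD of the change being compared. A two-sided 95% interval and a common SD are assumed.

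**Contrasts named.** Four of active against control and six among active arms, 4 + 6 = 10, all 4 against 4.

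**Standard error**, √(1/n₁ + 1/n₂):

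- 4 v 4: √(0.25 + 0.25) = √0.500 = 0.707
- 16 v 4: √(0.0625 + 0.25) = √0.3125 = 0.559
- Reduction: 1 − 0.559/0.707 = 21%. On the variance scale, 1 − 0.3125/0.500 = 37.5%.

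**95% half-width**, t × SE:

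| Basis | 4 v 4 | 16 v 4 | Narrower by |
|---|---|---|---|
| Own degrees of freedom (6 and 18) | 2.447 × 0.707 = 1.73 | 2.101 × 0.559 = 1.17 | 32% |
| Five-arm residual variance (20 − 5 = 15) | 2.131 × 0.707 = 1.51 | 2.131 × 0.559 = 1.19 | 21% |

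The second row is the like-for-like comparison. In the first row, part of the gain comes from having 18 degrees of freedom instead of 6.

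The pooled estimate needs no separate model. The mean of the four active-arm means minus the control mean has variance (1/16)(4 × 1/4) + 1/4 = 0.3125, the same as above.

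**Dilution.** Suppose k of the four active arms have an effect of 1 SD and the rest have none. The pooled signal-to-SE ratio is (k/4)/0.559. A responding arm alone against control has 1/0.707 = 1.41.

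| Arms responding | Pooled | One responding arm v control |
|---|---|---|
| 1 | 0.45 | 1.41 |
| 2 | 0.89 | 1.41 |
| 3 | 1.34 | 1.41 |
| 4 | 1.79 | 1.41 |

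Put another way, pooling wins over a given arm only if the average effect across the four arms is at least 0.559/0.707 = 79% of that arm's effect.

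**Leukapheresis.** Intervention description {11a} places leukapheresis at day −8 in the active arms. For controls, "Standard care involves no leukapheresis visit and no administration of TolDC_CitPep_ but all other study procedures remain the same". Any active-versus-control contrast, pooled or by arm, therefore includes whatever leukapheresis does to the day-0 sample and to change from it. Contrasts among active arms do not carry this difference. In Table 2, Set 1 (screening) and Set 3 (baseline) include a full blood count in all participants; Set 2, taken at the leukapheresis visit, excludes controls.

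**The case against.** The strongest reply is that the primary objective is not left without an analysis. The Objectives section says the objectives are met by comparing baseline with follow-up, and the longitudinal analysis is not restricted to single arms, so it could use all 16 treated participants. This stands. A reader might infer that the plan makes only four-versus-four comparisons, or that nothing addresses the primary objective; the document supports neither. What remains is that this sentence mentions no control comparison, and the mixed model is described only as a source of variability estimates.

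The analysis plan is not shown and may add a pooled contrast; nothing in the article rules one out. That limits the point to a recommendation on the contrasts the article names. The inconsistent wording on objectives and adequacy is in the article whatever the analysis plan contains.

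Pooling also has a real cost. It spans three routes and a 100-fold dose range (10^5 to 10^7), and the authors expect direct nodal injection to be the route most likely to reach a lymph node. The stated design aim is to demonstrate and to compare. Arm-level comparison is a defensible choice, and a reader should not infer that the pooled contrast must come first or replace it.

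A reader might also want to argue from power, smallest attainable p-values or a count of comparisons. The plan disclaims formal testing, and Outcomes {12} speaks of selecting among modalities, so the number of comparisons is not fixed. Those arguments do not measure a loss in what is planned. Finally, the adequacy remark sits in a sentence that lists small numbers as a limitation, and nowhere does the article claim equivalence or a ranking of routes.

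**Conclusion.** The point holds as one about estimation. Among the between-arm contrasts named, none matches the route-free primary objective, and adding the 16-versus-4 estimate is nearly free. The gain is 21% on the standard error, and 21% or 32% on interval width depending on the variance estimate. A loss of about a third is correct only for interval width with separate degrees of freedom (32%) or, roughly, for information (37.5%), so it should not be quoted without the scale.

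The figures assume that all 20 participants are analysed, a common SD, and broadly similar effects across active arms. If product fails release or participants drop out, intervals widen. The effect of baseline adjustment cannot be quantified from the document.

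Separately, the Discussion conflicts with Table 1 on the status of route comparison, and the adequacy statement has no support beyond feasibility. With half-widths of 1.5 to 1.7 SD between two arms, neither a ranking of routes or doses nor equivalence could be concluded.

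**What to change.** 1. In Statistical methods {20a}, add a pooled all-TolDC (16) versus control (4) estimate of baseline-adjusted change with a 95% interval, for each primary biomarker analysed. Keep all arm-level estimates beside it, and say that pooling is informative only if effects are broadly similar across arms.
2. Align the Discussion with Table 1 on the exploratory status of route and dose comparison.
3. In the Abstract and Discussion, replace the adequacy statement with the achievable half-widths (about 1.2 SD pooled; 1.5 to 1.7 SD between two arms). State that no ranking or equivalence of routes or doses will be concluded.
4. State that every active-versus-control contrast, including those already planned, carries any effect of leukapheresis. Compare the screening-to-baseline change in blood counts between active and control participants as a check. It is only partial: a full blood count does not measure the immune endpoints, and the screening interval varies.

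The cost is one extra contrast and some rewording, with no new participants, visits or samples. The statistical risk is dilution if few arms respond, which the retained arm-level estimates would help to reveal.
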